### Sample size calculations

Sample size for primary clinical outcome of unscheduled care within the previous year.

In our preliminary work, we found an unscheduled care rate of 34% [35]. We chose an absolute difference of 7% (from 34 to 27%) between trial arms as being the minimum important effect clinically and to health services. This is approximately half the effect achieved in effectiveness trials of supported self-management [6]. To detect this difference with 90% power and 5% significance level, 1868 patients would be required in an individually randomised trial without clustering.

Assuming an intraclass correlation (ICC) of 0.07 (taken from experience of pragmatic implementation studies, and supported by our analysis of data from 379 OPC practices) and assuming 200 individuals/practice, we need 70 practices (14,000 patients) in each group (increased to 72 practices/arm to allow for practice withdrawal) to detect the minimum important effect with 90% power and 5% significance level. Patients will only be included in the analysis dataset if they have ‘active asthma’ with the same practice at baseline, 12 months and 24 months follow-up, which avoids individual patient attrition. We originally intended to limit recruitment to practices with a list size > 6000 (assuming 6% will have active asthma [65]) to avoid cluster sizes < 200 (and randomly sampling if clusters were > 200). During recruitment, it became clear that this excluded many small rural general practices in Scotland, so we opted to allow variable cluster sizes (including a few clusters likely to be < 200). Furthermore, the COVID-19 pandemic resulted in a reduction in asthma attacks [66, 67], and an analysis of the OPC dataset (*n* = 286 practices) in September 2021 showed that 25.8% was a more realistic estimate of the proportion with unscheduled care that we could expect in the control group. Maintaining the recruitment target of 144 practices (140 after loss to follow-up) and allowing for a variable cluster size (mean = 200; coefficient of cluster size variation = 0.8), the study would have 94.7% power to detect a reduction from 25.8 to 18.8%.

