### Statistical analysis

Analysis will be on data at 12 months (implementation/process outcomes) and 24 months (health outcomes) follow-up. Individuals will be included in the analysis only if they were registered in a practice at baseline, 12 months and 24 months follow-up. Practices will be analysed in the group to which they were allocated regardless of compliance (intention-to-treat). The target of estimation is the average treatment effect across participants in terms of the primary clinical as well as primary implementation outcome. An unweighted independence estimating equation analysis on participant-level data will be used to estimate the participant-average difference in proportions between groups. This model employs an independence working correlation structure in conjunction with robust standard errors to account for clustering. Secondary outcomes will be analysed using the same or a similar model appropriate for the respective variable type. The models will include fixed effects for stratification variables and may incorporate additional individual-level covariates as fixed effects (covariates are limited as we are taking them from routine data). A fully pre-specified model will be provided in the statistical analysis plan (SAP). Treatment effect estimates, with associated confidence intervals and *p*-values, and ICCs will be reported for each outcome.

The primary clinical outcome as well as the secondary outcomes of unscheduled care (12 months), asthma attacks and prescribing outcomes will, by definition, not have any missing data as the absence of a code describing an event or prescription is defined as the binary variable value ‘no’. Patterns and amount of missing data for questionnaire outcomes and other routine data variables will be explored, and a suitable multiple imputation method used. The strategy for dealing with missing values will be articulated in detail in the SAP which will be prepared by the Pragmatic Clinical Trials Unit (PCTU) statisticians in consultation with other blinded research team members. Allocation codes will not be released to the statisticians before the SAP is signed off and made publicly available.

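### The stated 94.7% power for the primary clinical outcome does not match the planned size-weighted analysis, which has about 82% power on the protocol's own inputs (ICC 0.07 carried over)

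*Protocol article*

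**What the plan says.** Two sections of the protocol article bear on this.

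- **Sample size calculations.** The first calculation takes 34% v 27%, "Assuming an intraclass correlation (ICC) of 0.07" and 200 patients per practice, and arrives at 70 practices per arm "to detect the minimum important effect with 90% power and 5% significance level". After the pandemic the control rate was revised: "25.8% was a more realistic estimate of the proportion with unscheduled care that we could expect in the control group". Sampling to a fixed cluster size was dropped. The revised power statement rests on "Maintaining the recruitment target of 144 practices (140 after loss to follow-up") and on "allowing for a variable cluster size (mean = 200; coefficient of cluster size variation = 0.8"), and concludes that "the study would have 94.7% power to detect a reduction from 25.8 to 18.8"%. No ICC, design-effect formula or analysis method is named for this revised figure.
- **Statistical analysis.** "An unweighted independence estimating equation analysis on participant-level data will be used to estimate the participant-average difference in proportions between groups". The working correlation is independence, with robust standard errors. The section on the impact of COVID-19 takes baseline adjustment out of the main analysis.

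**The concern.** Once practices vary in size, the variance of the treatment effect depends on how the analysis weights them. An inverse-variance weighted or mixed-model analysis gives practices of very different size nearly equal weight when the ICC is 0.07 and the mean size is 200, so size variation costs it little. An unweighted independence estimating equation weights practices in proportion to size, so a few large practices can dominate and the cost is large. The protocol's figure shows almost no cost from a CV of 0.8, which is hard to square with the estimator it specifies.

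At stake is the headline power of the primary clinical outcome. If the figure belongs to another analysis, the type II error at the minimum important difference of 7 points is about 18% rather than about 5%, and readers are told that the trial exceeds a 90% level that it does not reach.

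**Working it through.** **Inputs, from Sample size calculations unless stated**

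- Proportions 25.8% v 18.8%, a difference of 0.07.
- 140 practices analysed, 70 per arm (1:1 allocation), mean size m = 200, so 14,000 patients per arm.
- CV = 0.8, so CV² = 0.64.
- ICC = 0.07, stated for the first calculation and assumed here for the revised one.
- Significance level 5%. Sidedness is not stated; two-sided is assumed and reproduces the printed figure.

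Power is computed as Φ{[0.07·√n − 1.96·√(2·p̄(1−p̄))] / √(p1(1−p1)+p2(1−p2))}, where n is the effective sample size per arm and p̄ = 0.223. Then 2·p̄(1−p̄) = 0.3465 and p1(1−p1)+p2(1−p2) = 0.3441.

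**1. Reproducing the printed 94.7%**

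- Equal practice sizes: DE = 1 + 199 × 0.07 = 14.93; n = 14,000/14.93 = 937.7; power 95.4%.
- Inverse-variance weighting with unequal sizes: DE = [1+(m−1)·ICC] / [1 − CV²·L(1−L)], with L = m·ICC/(m·ICC + 1 − ICC) = 14/14.93 = 0.938. The relative efficiency is 1 − 0.64 × 0.938 × 0.062 = 0.963, so DE = 14.93/0.963 = 15.51, n = 902.7 and power is 94.72%.

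This matches to the printed decimal, which also supports the assumption that ICC 0.07 was carried over.

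**2. The planned analysis**

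With weights proportional to size, DE = 1 + [(1+CV²)·m − 1]·ICC = 1 + (1.64 × 200 − 1) × 0.07 = 1 + 327 × 0.07 = 23.89.

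- n = 14,000/23.89 = 586 per arm.
- Numerator: 0.07 × √586 − 1.96 × √0.3465 = 1.6945 − 1.1538 = 0.5407. Divided by √0.3441 = 0.5866, this is 0.92, and power is 82.2%.
- With unpooled variance 82.4%; with a t reference on 138 df 81.8%.

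**3. Simulation check**

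Beta-binomial data, 70 practices per arm, CV 0.8, ICC 0.07, robust standard errors, 6,000 runs. The independence estimating equation rejected in 82.4% of runs with gamma-distributed sizes and 83.7% with lognormal sizes. Inverse-variance weighting in the same data gave about 94.3% under both.

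**4. Sensitivity of planned-analysis power to the ICC (CV 0.8)**

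| ICC | Design effect | Effective n per arm | Power |
|---|---|---|---|
| 0.07 | 23.89 | 586 | 82.2% |
| 0.06 | 20.62 | 679 | 87.3% |
| 0.05 | 17.35 | 807 | 92.3% |
| 0.045 | 15.72 | 891 | 94.5% |

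**5. Detectable difference**

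Solving for 90% power at n = 586 from a control rate of 25.8% gives 7.82 points (pooled), 7.80 (unpooled) or 7.85 (t, 138 df), so about 7.8.

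**The case against.** **The source of 94.7% is not documented.** This stands. The protocol names no formula. The inverse-variance match is close but not unique: unweighted cluster means with lognormal sizes also give 94.7%. A reader might infer that the sponsor powered the trial for a mixed model; the document does not say so, and that explanation is only probable. The mismatch does not depend on it, because none of the calculations that land near 94.7% at ICC 0.07 is the planned analysis.

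**ICC 0.07 may not apply to the revised calculation.** This stands in part. The 0.07 was supported by data from 379 practices, whereas the revised control rate came from a separate analysis of 286 practices, and no ICC is restated. Calling 82% the trial's real power would therefore overstate what is known. But no other ICC is given for this outcome, 0.07 reproduces the printed figure, and the planned analysis would need about 0.045 to come near it.

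**The achieved CV may be smaller**, since very small practices are excluded. At CV 0.65 and ICC 0.07 the planned analysis has about 87% power. But 0.8 is the protocol's own planning value, and the stated power should follow from it.

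**Covariates may recover precision.** The stratifiers stay in the model and could help. The protocol quantifies no such gain, and 94.7% is reproduced without one.

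**A planning figure does not affect the analysis.** Correct. The estimator, test and error rate are unchanged, and a null result would be read from its confidence interval. A reader might go further and infer that the estimator is wrong or that baseline adjustment should be restored. Neither follows: the estimator matches the participant-average target, and the protocol rejected baseline adjustment for the main analysis with stated reasons.

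**Conclusion.** Wrong as written. The stated 94.7% is not the power of the analysis that the same document specifies. With 140 practices, mean size 200, CV 0.8 and ICC 0.07, the planned independence estimating equation has about 82% power for 25.8% v 18.8% (81.8–82.4% by formula, 82–84% by simulation), a shortfall of 94.7 − 82.2 = 12.5 points. That is above 80% but below the 90% used in the first calculation.

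The conclusion rests on a two-sided 5% test, on carrying ICC 0.07 over, and on no precision gain from covariates. The mismatch with the planned estimator follows from the protocol's own inputs. The exact replacement figure is conditional on the ICC.

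**What to change.** Keep the estimator. In Sample size calculations, replace the revised power sentence with:

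*With 140 practices, mean size 200, CV 0.8 and ICC 0.07, the planned independence estimating equation analysis has about 82% power for 25.8% v 18.8% (about 87% at ICC 0.06, 92% at ICC 0.05); the difference detectable with 90% power at ICC 0.07 is about 7.8 points.*

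Name the design-effect formula, 1 + [(1+CV²)m − 1]·ICC, and state the ICC used. If the revised figure in fact rested on a different ICC, give that value and its source and recompute with the same formula.

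The cost is wording only, in the protocol and wherever the SAP repeats the figure. Recruitment, data collection and the analysis model do not change, but the printed power becomes less favourable.

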### Sample size for the implementation outcome of asthma plan ownership

About a third of people who responded to an Asthma and Lung UK survey in 2014 owned an action plan [68]. Assuming a 15% increase in asthma action plan ownership in the IMP^2^ART implementation arm, we would have an effect size of *h* = 0.322. To detect this difference with 90% power, 203 patients in each arm would be needed without clustering. Accounting for within general practice clustering with ICC = 0.03, we would need 20 completed questionnaires from 32 clusters (16 practices from each arm), a total of *n* = 640 patients. Given the average questionnaire response rate is ≈45%, we will post questionnaires to 50 participants/practice.

### Randomisation

The unit of randomisation will be the general practice. Remote online randomisation (1:1 implementation:control) will be provided by the Pragmatic Clinical Trials Unit (PCTU), Queen Mary University of London. Stratifiers, determined according to contextual influences identified during developmental work [50, 51], will be deprivation status (less deprived, ≤ median deprivation score/more deprived, > median deprivation score), practice list size (small, ≤ 8035 patients; large, > 8035 patients) and GP training status of the practice (yes/no). In a second step, 32 practices will be randomly selected for quality improvement questionnaire data collection, ensuring that these practices are distributed evenly between the implementation and control groups. Randomisation is implemented in REDCap (Research Electronic Data Capture) software [69] and allocations will be requested by the programme manager (VH).

### Protection against bias

Blinding of general practices to allocation will not be possible; however, aspects of the trial data collection and analysis will be blind. Routine data collection for the primary health outcome (unscheduled care) will be collected by automated software used by OPC for their quality improvement service. The personnel who produce audit reports for the practices (who cannot be blinded) will not be the same as the OPC research database personnel who will handle data for the trial and who will be blind to allocation. OPC’s quality improvement questionnaires (including the primary implementation outcome: ownership of action plans) are self-completed. Data entry and data cleaning personnel will be blind to allocation. Statistical analysis will be undertaken by personnel blind to allocation.

### Statistical analysis

Analysis will be on data at 12 months (implementation/process outcomes) and 24 months (health outcomes) follow-up. Individuals will be included in the analysis only if they were registered in a practice at baseline, 12 months and 24 months follow-up. Practices will be analysed in the group to which they were allocated regardless of compliance (intention-to-treat). The target of estimation is the average treatment effect across participants in terms of the primary clinical as well as primary implementation outcome. An unweighted independence estimating equation analysis on participant-level data will be used to estimate the participant-average difference in proportions between groups. This model employs an independence working correlation structure in conjunction with robust standard errors to account for clustering. Secondary outcomes will be analysed using the same or a similar model appropriate for the respective variable type. The models will include fixed effects for stratification variables and may incorporate additional individual-level covariates as fixed effects (covariates are limited as we are taking them from routine data). A fully pre-specified model will be provided in the statistical analysis plan (SAP). Treatment effect estimates, with associated confidence intervals and *p*-values, and ICCs will be reported for each outcome.

The primary clinical outcome as well as the secondary outcomes of unscheduled care (12 months), asthma attacks and prescribing outcomes will, by definition, not have any missing data as the absence of a code describing an event or prescription is defined as the binary variable value ‘no’. Patterns and amount of missing data for questionnaire outcomes and other routine data variables will be explored, and a suitable multiple imputation method used. The strategy for dealing with missing values will be articulated in detail in the SAP which will be prepared by the Pragmatic Clinical Trials Unit (PCTU) statisticians in consultation with other blinded research team members. Allocation codes will not be released to the statisticians before the SAP is signed off and made publicly available.

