### Outcomes

#### Primary clinical outcome: unscheduled asthma care (second year post-randomisation)

The primary clinical outcome is the proportion of clinically eligible patients with at least one episode of unscheduled care for asthma in the second year after randomisation (supported self-management will be targeted by the implementation strategy during the first year post-randomisation, thus, impact on unscheduled care will not be apparent until the second year). Unscheduled care is defined as the proportion of people (≥ 5 years of age) with at least one unscheduled asthma consultation (GP consultation; and/or out-of-hours attendance; A&E attendance; hospital admission) during the second year in the trial (i.e. between 12 and 24 months post-randomisation). The primary clinical outcome will be measured using routine coded data extracted by OPC at 24 months from clinically eligible patients on the ‘active asthma’ register of participating practices. As there is considerable annual turnover in the ‘active asthma’ register (20% per year in one practice [59]), we will only include patients who have been on the ‘active asthma’ register of the practice at baseline, 12 months and 24 months.

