#### Primary implementation outcome: ownership of action plans at 12 months

The primary implementation outcome is the proportion of patients with an action plan. We will measure action plan ownership by a quality improvement questionnaire mailed to 50 patients randomly selected from the clinically eligible population in 32 randomly selected practices (16 practices in each trial arm). Ownership of an action plan is defined as the proportion of people (≥ 5 years of age) who respond ‘Yes’ to the question ‘Has your asthma nurse or doctor provided you with an asthma “action plan”?’ in the OPC quality improvement questionnaire mailed at 12 months. The questionnaire will be mailed, with one reminder sent by SMS.

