### Impact of the COVID-19 pandemic on outcomes

In addition to affecting trial timelines and requiring intervention modifications the pandemic also had an impact on trial outcomes and consequently the statistical analysis. Restrictions on movement and interaction with people outside of one’s household were imposed leading to reduced viral spread and reduced access to healthcare (the public were encouraged to access healthcare only when absolutely necessary) [66, 67]. There is also evidence [66] of increased demand for preventer medication at the onset of the lockdown (March 2020) though whether this represents improved adherence to medication or stockpiling is unclear. Our analysis of a large dataset provided by OPC research database confirmed marked changes in primary and secondary outcomes in the first year of the pandemic compared to the prior year.

The original intention was that statistical analysis models would adjust for baseline, that is, the 12 months prior to randomisation. The main analysis of outcomes has now been changed to models not adjusting for baseline as the effect of the pandemic on baseline outcomes will differ for clusters. For practices recruited earlier, the baseline period will overlap with the pandemic and associated restrictions to a large extent whilst for practices recruited later there were fewer, if any, restrictions (note that there were also regional variations in restrictions). Consideration was given to using the 12-month period prior to the pandemic as the baseline. This was also rejected as (a) the time period between baseline and follow-up would vary for clusters and (b) for participants to be included in the study data they would have to be a registered patient with that practice at all three time points, and this longer overall time period would have reduced the sample size. However, data will be extracted from the 12 months before the start of the pandemic until the 24 months follow-up ends and three sensitivity analyses will be conducted—a model adjusting for baseline at the individual level, a model adjusting for baseline at the individual level using the 12 months before the pandemic as the baseline period, and a repeated measures model using baseline, 12-months and 24-month follow-up.

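### The 24-month registration rule is not limited to 24-month outcomes, so as written it also removes valid 12-month action-plan questionnaires

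*Protocol article*

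**What the plan says.** The Statistical analysis section opens by naming two sets of analyses: "Analysis will be on data at 12 months (implementation/process outcomes) and 24 months (health outcomes) follow-up". The next sentence sets a single rule for both: "Individuals will be included in the analysis only if they were registered in a practice at baseline, 12 months and 24 months follow-up". The same paragraph goes on to define the target of estimation for the primary clinical and the primary implementation outcome together. The section on the impact of COVID-19 repeats the condition for inclusion in the study data: "they would have to be a registered patient with that practice at all three time points".

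The outcome-specific sections are narrower.

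- **Clinically eligible patient population** defines eligibility without any 24-month condition. It adds continuous membership of the active-asthma register only for the primary health outcome.
- **Primary clinical outcome** gives the three-time-point rule for that outcome and explains it by register turnover, put at "20% per year in one practice".
- **Sample size calculations** gives the same condition for the clinical outcome: "only be included in the analysis dataset if they have ‘active asthma’ with the same practice at baseline, 12 months and 24 months follow-up".
- **Primary implementation outcome** draws 50 patients per practice from the clinically eligible population. It defines ownership by a Yes answer "in the OPC quality improvement questionnaire mailed at 12 months" and sets no 24-month condition.
- **Sample size for the implementation outcome** allows for non-response only: "Given the average questionnaire response rate is ≈45%, we will post questionnaires to 50 participants/practice".

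**The concern.** Ownership is fixed when the questionnaire is answered at 12 months. Whether the respondent is still registered a year later adds nothing to that answer. Under the general rule, a valid return is nevertheless removed if the patient has left by 24 months.

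Two things are at stake. The first is selection. The exclusion depends on an event after both randomisation and outcome measurement, so the analysed respondents are no longer simply those who were sampled and replied. If the condition is taken as staying on the active-asthma register, as the clinical outcome sections have it, it requires a recent asthma prescription. A strategy that promotes reviews and self-management could plausibly influence that. The second is precision on a primary outcome, because the number mailed was set with non-response in mind and nothing else.

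The other 12-month outcomes fall under the same rule: the further questionnaire measures (GINA control in the sub-group, and confidence in self-management), first-year unscheduled care, asthma reviews, and recorded action plan provision at 12 months.

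**Working it through.** **Inputs.** The implementation sample size section gives h = 0.322, 90% power, ICC 0.03, 16 practices per arm, 20 completed questionnaires per practice, 50 mailed and about 45% response. The 5% significance level is stated for the clinical outcome; I assume the same level, two-sided, here. The share lost between 12 and 24 months, t, is not given for questionnaire respondents. The only related figure is 20% yearly turnover of the active-asthma register in one practice, so I take t from 10% to 25%.

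**Reproducing the plan.**

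- Without clustering: n per arm = 2 × ((1.960 + 1.282) / 0.322)² = 202.7, so 203, as stated.
- Design effect at 20 per practice: 1 + 19 × 0.03 = 1.57.
- Practices per arm: 203 × 1.57 / 20 = 15.9, so 16, giving 32 × 20 = 640 in total, as stated.
- Power = Φ(h × √(n_eff / 2) − 1.96), with n_eff = 16m / (1 + (m − 1) × 0.03) for m returns per practice. At m = 20, n_eff = 320 / 1.57 = 203.8 and power is 90.2%.

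**Effect of the rule.** Expected analysable returns per practice are m = 50 × 0.45 × (1 − t).

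| Loss t | Returns per practice | Total (32 practices) | Power |
|---|---|---|---|
| 0% (rule not applied) | 22.5 | 720 | 92.0% |
| 10% | 20.25 | 648 | 90.4% |
| 15% | 19.1 | 612 | 89.4% |
| 20% | 18.0 | 576 | 88.2% |
| 25% | 16.9 | 540 | 86.8% |

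For example, at t = 20%, n_eff = 16 × 18 / (1 + 17 × 0.03) = 288 / 1.51 = 190.7, and power = Φ(0.322 × √95.4 − 1.96) = Φ(1.18) = 88.2%.

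**Break-even.** The target of 20 is met while 22.5 × (1 − t) ≥ 20, that is up to t = 1 − 20 / 22.5 = 11.1%. At t = 20%, keeping 20 would need 20 / (0.45 × 0.8) = 55.6, so 56 mailed per practice.

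**The case against.** The best reply is that the rule was never meant for the questionnaire. Three sections tie it to the clinical outcome, the questionnaire section has no such condition, and a sample size that ignores later loss may itself show that none was expected. No section describes matching returns to 24-month registration. This is a fair account of probable intent, and it means a reader should not conclude that returns will in fact be discarded. It does not cure the wording: the analysis section, where an analyst looks for the analysis set, states the rule without limit directly after naming the 12-month outcomes.

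A reader might also infer that a fifth of returns would go. The documents do not support that as a firm figure. The 20% comes from one practice and concerns the active-asthma register, whereas the analysis section says registered in a practice. A patient can leave the register and stay on the practice list, and people who answer questionnaires may move less than average.

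Nor do the documents show bias. A link between leaving and arm is plausible, but nothing gives its direction or size.

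Finally, a common closed cohort has real merit for routine-data outcomes. They are assessed at baseline, 12 and 24 months, and a repeated measures model over these times is planned as a sensitivity analysis. Keeping the same patients throughout is a defensible choice there, so this part of the objection stands.

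**Conclusion.** The point holds as an inconsistency that affects a primary outcome. As written, the inclusion rule conditions 12-month action plan ownership on registration a year after measurement, in conflict with the sections that confine the condition to the primary clinical outcome.

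The loss of power is modest: from 92.0% to 88.2% at 20% loss, which is under 2 points below the 90% target. At 10% loss the target is still met. These figures rest on the plan's h, ICC and response rate, a two-sided 5% level, and an assumed loss for which the documents give only indirect evidence. The stronger reason to correct the rule is that it selects on a post-randomisation event with no gain for the questionnaire outcome. That is a risk of bias, not a demonstrated one. The point does not extend to calling the three-time-point cohort wrong for the routine-data secondary outcomes.

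**What to change.** Amend the inclusion sentence in the Statistical analysis section so that registration at 24 months is required for the 24-month outcomes only, and bring the COVID-19 section's statement about the study data into line. State that the 12-month questionnaire outcomes, including action plan ownership, are analysed in all respondents who were clinically eligible at baseline and registered with the practice at 12 months.

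For 12-month secondary outcomes from routine data, the three-time-point cohort may be kept for comparability with the primary analysis. If so, say this explicitly and add a sensitivity analysis in patients registered at baseline and 12 months.

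The cost is one sentence in the protocol, carried into the SAP, plus slightly different populations for the 12-month and 24-month outcomes. No new data collection is needed, and the wording can be settled before the SAP is signed off and allocation codes are released.

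### With a fixed 50 patients mailed per sampled practice, the unweighted analysis of action-plan ownership estimates roughly a practice-average effect, not the participant-average effect the protocol names

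*Protocol article*

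**What the plan says.** Under Statistical analysis, the article gives a single target: "The target of estimation is the average treatment effect across participants in terms of the primary clinical as well as primary implementation outcome". The next sentence fixes the estimator: "An unweighted independence estimating equation analysis on participant-level data will be used to estimate the participant-average difference in proportions between groups". Clustering is handled by robust standard errors. Stratification variables enter as fixed effects, and secondary outcomes use the same or a similar model.

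The section on the primary implementation outcome says that the questionnaire is "mailed to 50 patients randomly selected from the clinically eligible population in 32 randomly selected practices", 16 per arm. The matching sample size section repeats the fixed number: "we will post questionnaires to 50 participants/practice". Under Randomisation, the practices are chosen at random: "In a second step, 32 practices will be randomly selected for quality improvement questionnaire data collection". Selection in proportion to size is not mentioned, nor is a number mailed that depends on size, nor a sampling weight.

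Practice size varies by design (Practice eligibility criteria and recruitment). The sample size section for the clinical outcome plans on a mean of 200 patients per practice and a coefficient of variation (CV) of 0.8.

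**The concern.** An unweighted independence estimating equation gives every analysed patient the same weight. This yields the participant-average effect when all eligible patients are analysed, or when every practice is sampled at the same rate. The first condition holds for unscheduled care, which is assessed on the whole eligible population, so each practice counts by its size.

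Neither condition holds for action-plan ownership. With 50 mailed per sampled practice, a patient in a practice with 200 eligible patients has a 25% chance of being mailed (50/200). In a practice with 400 the chance is 12.5% (50/400). Large practices are under-represented relative to their patients, and nothing in the stated analysis corrects for that.

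At stake is the meaning of a primary outcome. The result would be reported as an average over patients when it is close to an average over practices. The two primary outcomes would carry one label for two different quantities.

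**Working it through.** **Inputs from the article**
- 32 practices, 16 per arm; 50 mailed per practice; response about 45%; 20 completed questionnaires per practice planned, 640 in total.
- ICC 0.03; h = 0.322; 90% power; 203 per arm before clustering. Alpha is not restated for this outcome; I take 5% two-sided, as for the clinical outcome.
- CV of practice size 0.8. This is a planning value for the clinical outcome across all practices, borrowed here for the 32.

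**Assumed, not in the article:** the SD of the effect across practices and its correlation with practice size.

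**1. The plan's own sample size**
- n per arm = 2 × ((1.960 + 1.282)/0.322)² = 202.7, so 203.
- Design effect = 1 + (20 − 1) × 0.03 = 1.57.
- 202.7 × 1.57 = 318.2; 318.2/20 = 15.9, so 16 practices per arm and 640 patients.
- Power with 320 per arm = Φ(0.322 × √(320/1.57/2) − 1.96) = 90.2%.

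The stated figures reproduce. They belong to an analysis with equal numbers per practice and no weights.

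**2. Weight that each practice receives**
- Expected returns are 50 × 0.45 = 22.5 per practice, whatever its size. In a complete-case analysis each practice has about 1/16 of its arm's weight, varying with its response rate.
- If non-responders among the 50 are multiply imputed, each practice contributes 50 and the weights are exactly equal.
- In neither case does weight follow practice size. List size enters the model only as a two-level main effect, which adjusts the comparison but does not restore patient weights.

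**3. Gap between the two effects**

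Let N be the eligible patients in a practice and D the effect there.
- Participant-average = ΣND/ΣN; practice-average = mean(D).
- Difference = cov(N, D)/mean(N) = CV × corr(N, D) × SD(D).

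Absolute gap in percentage points at CV 0.8:

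| \|corr\| | SD 5 | SD 10 | SD 15 |
|---|---|---|---|
| 0 | 0 | 0 | 0 |
| 0.3 | 1.2 | 2.4 | 3.6 |
| 0.5 | 2.0 | 4.0 | 6.0 |

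**4. Check by simulation (assumed scenario)**

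Lognormal sizes with mean 200 and CV 0.8; effect +20 points in the smaller half of practices and +10 in the larger half. The larger half holds 75.9% of patients.
- Practice-average: 15.0 points.
- Participant-average: 0.241 × 20 + 0.759 × 10 = 12.4 points.
- With 16 practices per arm, 50 mailed, 45% response and ICC 0.03, the unweighted estimate averaged 14.9 (SD 4.8) and the size-weighted estimate 12.5 (SD 5.8).

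This is a strong dependence on size. The SD of the effect is 5 points, so the implied |corr| is 2.6/(0.8 × 5) = 0.65. It confirms the mechanism and is not a forecast.

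**5. Precision of a weighted analysis**

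Weighting an equal take by practice size multiplies the design effect by about 1 + CV². Power at h = 0.322 with 320 per arm:

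| CV | Design effect | Effective n per arm | Power |
|---|---|---|---|
| 0 | 1.57 | 203.8 | 90% |
| 0.4 | 1.57 × 1.16 = 1.82 | 175.7 | about 85% |
| 0.6 | 1.57 × 1.36 = 2.14 | 149.9 | 80% |
| 0.8 | 1.57 × 1.64 = 2.57 | 124.3 | 72% |

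The factor 1.64 is a large-sample value. The simulated SDs imply (5.8/4.8)² = 1.46. The design effect is then 1.57 × 1.46 = 2.29, the effective n about 140 and power about 77%. Hence 72–77% at CV 0.8.

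**The case against.** **The word participants may mean those mailed.** No individual patients are recruited, and the sample size section uses the word for questionnaire recipients. On that reading the unweighted analysis does average over participants. This reading is the weaker one: the recipients are drawn from the clinically eligible population, and one target is set for both outcomes. If it were intended, one label would still describe two different quantities.

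**The SAP may settle it.** It cannot do so quietly. Adding weights there would contradict the article's unweighted analysis, and changing the target would contradict the target sentence.

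**The two effects may coincide.** This stands. If the effect of the strategy is unrelated to practice size, the gap is zero. List size was made a stratifier because of contextual influences, which shows that it was thought relevant. It does not show that it modifies the effect.

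**Stronger readings that the document does not support**
- A reader might infer that the trial has about 70% power for this outcome instead of 90%. The lower figures belong only to a weighted analysis that the protocol does not plan, at a borrowed CV. The planned analysis keeps its 90% at the stated h. (Whether h = 0.322 fits a one-third baseline plus 15 points is a separate matter and should not be mixed in.)
- A reader might infer a known bias of several points. The SD and the correlation are assumptions.
- A reader might infer that the mismatch breaks an analysis linking ownership to unscheduled care. The Statistical analysis section plans no such analysis, and the two outcomes already differ in practices, timing and data source.
- The fixed 50 applies to the 32 sampled practices, not to all 144.

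**Conclusion.** The point holds as a mismatch between a stated target and a stated estimator. For action-plan ownership, and for the other questionnaire outcomes analysed with the same model, the unweighted analysis does not in general estimate the participant-average effect in the clinically eligible population. It estimates approximately the practice-average effect, with exactly equal practice weights only if all 50 mailed are analysed.

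The mechanism is certain given the text; its numerical effect is unknown and may be nil. The 0 to 6 point range rests on the borrowed CV of 0.8, |corr| of 0 to 0.5 and an SD of 5 to 15 points. The unweighted estimate remains a legitimate quantity, and the planned sample size is sound for it on the article's own h. What needs correcting is the label, together with the absence of any analysis that reaches the stated target.

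**What to change.** 1. For questionnaire outcomes, state the target as (approximately) the practice-average effect. Keep the participant-average target for the outcomes taken from routine data on all eligible patients.
2. Keep the unweighted analysis as primary for action-plan ownership.
3. Add a supplementary participant-average analysis. Weight each patient by the eligible patients in the practice divided by the patients analysed in that practice: responders in a complete-case analysis, the number mailed if non-responders are imputed. The numerator should be the count in the list from which the 50 were drawn.
4. Label the weighted analysis as supplementary because of its lower precision.

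The cost is a change of wording in the protocol and SAP and one extra model. No new patient data are needed, since eligible counts per practice should be available from the routine extraction. Making the weighted analysis primary would be expensive: 90% power at CV 0.8 would take 203 × 2.57/20 = 26.1, so 27 practices per arm instead of 16.
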